## Abstract

**Introduction:**

Pelvic fragility fractures (PFF) are common in older people and associated with a significant burden of mortality and morbidity. This is related to the challenges of appropriate pain control and early mobilisation. The current standard for treatment of PFF is non-surgical management. Minimally invasive surgical techniques for sacral fracture stabilisation have been shown to improve outcomes in terms of pain control and mobility, and they are safe. Randomised controlled trials are required before recommendations can be made for surgical management of PFF to become the new standard of care. This feasibility study will explore several uncertainties around conducting such a trial.

**Methods and analysis:**

ASSERT (Acute Sacral inSufficiEncy fractuRe augmenTation) is a single-site randomised controlled, parallel-arm, feasibility trial of surgical stabilisation versus non-surgical management of acute sacral fragility fractures in people aged 70 years and over. Patients will be randomised to either surgical or non-surgical group on a 1:1 ratio. Follow-up of participants will occur at 2, 4 and 12 weeks with safety data collected at 52 weeks. Primary objectives are to determine feasibility and design of a future trial, including outcomes on recruitment, adherence to randomisation and safety. This will be supplemented with a qualitative interview study of participants and clinicians. Secondary objectives will inform study design procedures to determine clinical and economic outcomes between groups, including scored questionnaires, analgesia requirements, resource use and quality of life data. Data analysis will be largely descriptive to inform outcomes and future sample size.

**Ethics and dissemination:**

Ethical approval was granted by the North East Newcastle and North Tyneside 2 Research Ethics Committee (reference 18/NE/0212). ASSERT was approved and sponsored by Nottingham University Hospitals NHS Trust (reference 18HC001) and the Health Research Authority (reference IRAS 232791). Recruitment is ongoing. Results will be presented at relevant conferences and submitted to appropriate journals on study completion.

**Trial registration number:**

ISRCTN16719542; Pre-results.

Strengths and limitations of this studyDescriptive analysis on effectiveness of outcomes will inform hypothesis testing in a future definitive trial, including levels of variability in order to power the trial appropriately.Nested semistructured interview study will provide valuable qualitative data to inform future definitive trial acceptability and processes.Determines the feasibility of economic measures including detailed resource use collection and quality of life data within the two arms, to aid the design of more comprehensive economic evaluation in a future definitive trial.The intervention is a proven safe surgical intervention, already used in existing healthcare practice, but further safety data in this cohort of patients will also be collected.A pragmatic trial set in an existing healthcare setting that may lead to a number of limitations on trial processes, including recruitment, adherence to randomisation and ease of data collection.

## Introduction

Pelvic fragility fractures (PFF) are common in older people, as they are a frequent presentation of osteoporosis, a condition characterised by low bone mass and structural deterioration of bone tissue, leading to bone fragility.^1^ Thus, PFF can occur as a result of low-energy trauma, typically following a fall from standing height or less.^2^ The reported overall incidence of PFF is variable, between 25 and 92 per 100 000 persons-years, with the highest frequency reported in females over the age of 75 years.^3–8^ Epidemiology studies worldwide have consistently shown a sustained increase in the age-adjusted incidence of PFF, with numbers expected to continue to rise exponentially over the next 10 years.^3 4 6 7 9–11^ These patients are also increasingly requiring inpatient admission for management of their PFF, representing a considerable ongoing burden to hospital services.^3 4 6 12^

The pelvis is a complex ring like structure composed of three principal bones; the paired innominate bones and the sacrum. Fractures of the pelvis are a heterogeneous group of fractures and are most commonly described by the Young-Burgess classification, which relates to the predominant direction of the vector force at the time of injury.^13 14^ Within this, lateral compression (LC) fractures are the most common and are further subtyped based on the resulting degree of displacement of the pelvic ring:^13^
Type I: Oblique or transverse ramus fracture and ipsilateral sacral compression fracture.Type II: Rami fracture and ipsilateral posterior ilium fracture dislocation (crescent fracture).Type III: Ipsilateral LC and contralateral anterior-posterior compression (windswept pelvis).

The most commonly identified PFF presenting to hospital is that of the anterior ring in the form of fractures of the pubic rami.^12 15 16^ 60%to 90% of these patients will also have a concomitant posterior ring fracture in the form of an insufficiency fracture of the sacrum.^2 17–19^ Type 1 LC is therefore the most common subtype of PFF.^17 20^ While anterior pelvic ring fractures can be identified on plain X-ray, those fractures of the posterior pelvic ring are most typically identified on CT or MRI, which now has a much wider availability on emergency admission to hospital.^17 19 21^ From a biomechanical point of view, an undisplaced anterior pelvic ring is more stable than a posterior pelvic ring fracture, with the posterior ring providing the majority of structure and stabilisation of the pelvis on load-bearing.^2^

PFF, especially those involving the sacrum within the load-bearing posterior pelvic ring, result in pain-related immobilisation and increased care dependency.^21–23^ PFF have been shown to confer poor outcomes like those reported extensively in hip fractures but covets much less attention.^24^ Inpatient 30-day mortality sits at up to 11%, with a 12-month mortality up to 27%.^5 9 12 15–17 20 24–26^ This may be related to the demographics of patients admitted to hospital with PFF. This patient group commonly has significant comorbidities and over a third exhibit cognitive impairment, leaving them more suspectable to the medical complications of pain-dependant immobility and associated prolonged hospital stay.^5 17 25^ Inpatient mortality is often attributed to exacerbation of pre-existing comorbidity.^12^ Around half of the patients admitted with PFF develop hospital and immobility related complications including pressure sores, infection, renal injury, venous thromboembolism and delirium.^9 16 17 25–28^ The majority are unable to return home at their baseline level of mobility or independence on discharge.^5 25 27^ In excess of this, those with confirmed combined anterior and posterior ring insufficiency fractures have hospital stays 2 weeks longer than those with isolated anterior ring fractures, higher complication rates, 30% more chance of losing previous independence and higher rates of institutionalisation.^17 20 22 29^

Current standard care for PFF is conservative, consisting of systemic analgesia and mobilisation as tolerated.^30^ As a response to the high level of associated morbidity, management of PFF needs to be targeted at good early pain control in order to allow early mobilisation, return of independence and discharge.^22 31^ Currently, standard pain management consists of the use of systemic analgesia, especially opioids, but pain control adequate to allow early mobilisation is difficult to achieve in this cohort.^23^ Barriers to adequate pain management in PFF can include under-reporting of symptoms due to cognitive impairment, susceptibility to side-effects of opioids in the elderly and undertreatment due to perceived prescriber fear of opioid side-effects.^32^

Development of minimally invasive surgical techniques targeting fractures of posterior ring sacral fractures may provide an alternative to improve adequate pain control in this significant subset of PFF.^21^ Minimally invasive keyhole surgery techniques involving percutaneous cement augmentation with or without trans-sacral screw are increasingly being performed in order to stabilise sacral fractures.^21 22 31^ For those patients who have failed to progress with conservative management, these procedures have been shown to reduce pain and the amount of analgesia required postoperatively.^30 33 34^ This in turn allows increased patient mobility with a quicker return to baseline function and shortened length of stay as well as having an established safety profile.^9 22 30 33–39^ However, there are no randomised controlled trials that compare efficacy of sacral fracture surgery compared with conservative management in the early stages of recovery.^21 22 33^

## Methods and analysis

### Aims

The aim of this study is to determine the feasibility and design of a future randomised controlled clinical trial to evaluate the clinical and cost effectiveness of keyhole spinal sacral fixation (cement augmentation±screw fixation) compared with current standard practice of non-surgical management in older people presenting in the early stages to hospital with a Type 1 LC PFF.

### Objectives

The feasibility and final design of a definitive trial will be determined by fulfilment of the objectives outlined below. These are to:Determine the number of patients who meet the eligibility criteria in addition to recruitment (including willingness to be randomised) and retention rates of randomisedpatients.Explore the adherence of clinicians to the randomisation of patients within the trial.To collect outcome measure data for the assessment of mobility, pain and quality of life (face to face and self-reported measures), for potential use in a future definitive trial; estimate the mean and SD of these quantitative measures for hypotheses testing purposes.Evaluate ease of access and availability of information from current primary and secondary care databases, to determine the most efficient way of measuring associated patient level resource use.Use a qualitative nested interview study to assess participants’ and clinicians’ views on trial acceptability and processes to inform the design and conduct of a future definitive trial.Evaluate long-term safety of the intervention.

### Study design

The primary study design is a parallel, two-arm randomised controlled feasibility trial with participants allocated to either surgical or non-surgical intervention on a 1:1 ratio. A preliminary economic evaluation and a qualitative nested interview study will also be embedded within the feasibility study.

Participants will be recruited from a single site, Queens Medical Centre (QMC), Nottingham University Hospitals NHS Trust (NUH), a university teaching hospital serving a population of 700 000 and offering a tertiary spinal surgical unit.

### Participants

Participants presenting to NUH with a Type 1 LC PFF who fulfil the eligibility criteria, outlined below, will be approached for possible recruitment into the study. A fragility fracture is defined as a fracture sustained after low level trauma, usually a fall from standing height or less.

#### Inclusion criteria

Aged 70 years and over.Ambulatory with/without walking aids prior to injury.Injury sustained within 28 days of presenting to hospital.

#### Exclusion criteria

Complex pelvic fractures (eg, fractures involving/or close to the hip joint) requiring urgent surgery or progressive weight bearing exercises.Pathological fracture in the context of known or unknown malignancy.Previous surgery of the pelvis with metal obstructing the planned paths of the iliosacral screws.Condition that precludes surgery or general/spinal anaesthesia.Bedbound prior injury.Receiving palliative care.Moribund on admission.

### Recruitment

All patients admitted with a Type 1 LC PFF as identified on imaging (CT or MRI) will be invited to participate. The research team will be notified of the potential participant and will confirm eligibility with their clinical care team. The process for obtaining participant informed consent will be in accordance with Good Clinical Practice guidance and will include consent for potential inclusion in the qualitative interview nested study.

An Abbreviated Mental Test (AMT) will be used as a screening tool for capacity assessment. If the admission AMT completed by the clinical team is documented as 5–6/10, then it will be repeated by the research team at the time of screening. A participant will be assumed to have capacity if their AMT≥7/10 at either point of assessment. An AMT<7/10 will prompt a capacity assessment based on the principles of the Mental Capacity Act 2005 in relation to research.

Relatives or carers of potential participants who are unable to provide consent independently, will be approached as the participants’ personal consultee. If there is more than one relative or carer willing to act as the patient’s consultee, then they must all agree on the decision for the participant to be included in the study.

For patients or consultees who decline to take part, they will be asked if they would be willing to share their reasons this. It will be made clear that this is in order to help us improve the design and acceptability of the study and there is no obligation to do this. The findings will be tabulated into the final results.

### Randomisation

Consented participants will be randomly allocated to either surgical intervention or conservative non-surgical care on the day they consent via a secure web-based system (Sealed Envelope Ltd) by a member of the research team, ensuring allocation concealment. In order to minimise bias, participant baseline enrolment data will be entered into the randomisation system to be stratified prior to intervention allocation. Randomisation to the intervention groups will be on a 1:1 basis.

### Interventions

*Intervention group* will receive surgical intervention by key-hole spinal sacral fixation as determined by the treating spinal surgeon based on the participant’s general condition, morphology of the fracture and surgeon’s experience. The surgery will be completed within 7 days of randomisation. Cement augmentation of the sacral ala will be undertaken in participants with unilateral or bilateral sacral fractures with minimal cortical comminution. Additional sacroiliac screw fixation will be offered to participants with extensive fracture patterns which affect both sacral ala with significant cortical comminution. Usual postoperative care, monitoring and rehabilitation will follow.

*Control group* will receive usual hospital care. Participants will be treated with appropriate analgesia and have regular input from the ward therapy team. Participants may be referred for surgical intervention if it is indicated by their clinical team. This will be recorded and data collected and followed up with intention to treat.

### Outcomes

The study procedures undertaken are directly related to the outcomes used in order to address the objectives of this feasibility study.

### Feasibility study outcomes

Primary outcomes:Number of eligible patients.Number of patients willing to be randomised and adherence to randomisation.Number of clinicians willing to randomise and adherence to randomisation.

Secondary outcomes:Rate of participant recruitment and retention.Data on the completeness and variability of proposed definitive trial outcome measures.Failure of non-surgical conservative care and adverse events (AEs) in both arms.

### Outcomes measures for the subsequent definitive trial

Primary outcome measures:Timed Up and Go test (TUG)^40^ as a measure of mobility requiring both static and dynamic balance.Roland Morris Disability Questionnaire (RMDQ)^41^ as a self-rated measure of physical disability caused by low back pain.

Secondary outcome measures:Abbreviated Mental Test (AMT) as an assessment of cognition.^42^
Montreal Cognitive Assessment (MoCA)^43^ as an assessment of cognition.Functional Independence Measure (FIM)^44^ as a measure of disability severity.Clinical Frailty Scale (CFS)^45^ as an assessment of frailty.Charlson Co-morbidity Index^46^ as a prediction of 1-year mortality based on comorbid conditions.Numeric 0–10 Pain Rating Scale^47^ as a measure of average pain on mobilising.EuroQol 5 Dimensions (EQ-5D-3L) Score^48^ as an assessment of quality of life.Barthel Activities of Daily Living (ADL) Index^49^ as an assessment of care dependency.Fracture details/classification.Analgesia requirements.Surgery details.Health and Social Care resource use.AEs and readmissions (as part of the long-term safety review).

### Analgesia requirement

Analgesia requirement will be recorded as follows: each medication will be classified as a strong opioid (including oxycodone, morphine, fentanyl, pethidine, hydromorphone, buprenorphine and tramadol), mild opioid (including medications containing codeine or dextropropoxyphene) or non-opioid medications (including paracetamol and non-steroidal anti-inflammatory drugs). The participant will be given a score of 0, 1 or 2 in each of these three categories depending on the number of concurrent different medications being taken within each category. Opioid medication will also include a calculation of the oral Morphine Equivalent Daily Dose using the Opioid Dose Equivalence score.^50^

### Study procedures

Participant flow through the trial is summarised in figure 1. Face to face contact with participants and/or carer will be required at baseline (considered day 0), week 2 and a limited number of participants at week 12. Telephone interviews will be conducted with participants at week 4 and for the majority of participants at week 12. Week 12 marks end of trial for the participant, with further contact made at week 52 as part of the long-term safety analysis.

**Figure 1 F1:**
[figure not shown]
Participant flow through the trial including timings of data collection.

Figure 2 shows the schedule of data collection, outlining which study procedures will be undertaken at what time point in the study period, measured from the point of randomisation. In addition, follow-up data at each time point will include participant still living, hospital length of stay, unplanned hospital readmission (within the first 28 days and 91 days post discharge) and all AEs, including surgical complications. For those participants that lack capacity, only clinically assessed questionnaires will be used. Participant contact will be conducted in the location the participant is residing at the time of the respective follow-up.

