### Sample size calculation

This feasibility study will aim to provide estimates of recruitment and retention rates, and the variability of important outcomes, in order to generate appropriate power calculations for the definitive trial. It is estimated that sample sizes between 24 and 50 are required for a feasibility study.^54–57^ Therefore, we propose to recruit for a 10-month period, from which we expect to screen approximately 100 patients. Our estimates are based on data from Gateshead Health Foundation Trust, who screened 67 patients with a similar eligibility criterion over a 12-month period within a smaller acute trust catchment population.^17^ We assume in this feasibility study that 20% of patients screened are not eligible and a 60% recruitment rate, so we expect to recruit 48 participants. By recruiting 48 patients, the estimated recruitment rate has a SE of 5.5% (95% CI 48.4% to 70.8%). Given the short active follow-up period, we are allowing for a lower 10% 3-month attrition rate. This estimates that 43 participants will complete the study, thus estimating the 90% retention rate with a SE of 4.4% (95% CI 77.3%; 96.5%). Completed follow-up on 43 patients will allow an estimated SE for the TUG of 1.2 s assuming the SD is about 8 s (95% CI 6.6 to 10.2) and an SE of 0.9 for the RMDQ, assuming the SD is about 6 (95% CI 4.9 to 7.6).

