### Health economic analysis

The within-trial economic evaluation will determine the cost-effectiveness of the surgical intervention compared with non-surgical (standard) treatment from an NHS and Personal Social Services perspective. The evaluation will follow the reference case guidance for technology appraisals as set out by NICE.^58^ Effectiveness will be captured using quality adjusted life years (QALYs) as assessed by the EQ-5D-3L.^48^ The primary outcome of the evaluation will be the incremental cost-effectiveness ratio (ICER) per additional QALY (ICER) gained from surgical fixation compared with standard care. Sensitivity analyses will be performed to control for uncertainty, which will include one-way and two-way sensitivity analyses on (but not exclusively) age, gender and baseline scores, with a probabilistic sensitivity analysis to control for all uncertainty. Results of the sensitivity analyses will be presented as tornado plots, 95% CI for the ICER and cost-effectiveness acceptability curves.

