The target cohort in question may also provide further recruitment barrier. Cognitive impairment is common (up to 67%) in older patients presenting to hospital with PFF.^5 17 25^ As these patients confer such a large proportion of the real world PFF cohort, it would severely affect the validity of the trial to exclude them. Therefore, we have included a consent process for those patients that lack capacity. Identification is by AMT as a surrogate marker of capacity, which is completed as part of the clinical assessment of all admitted patients and therefore does not add any unnecessary burden prior to recruitment. Patients without capacity are reliant on the presence of relatives or carers to act as personal consultees, which may add a logistics barrier and reduce the recruitment of this subset of participants. Participants with cognitive impairment that are recruited may also be less likely to complete data collection due to difficulty with engagement, introduce detection bias due to issues with recall and may be more likely to be lost to follow-up.

Even once randomised, our participants remain under the existing healthcare service’s care for the entirety of the trial and are therefore at risk of protocol deviations due to the pragmatic setting of the study. The final decision to receive any intervention remains the responsibility of the patient’s clinical teams. For participants in the surgical intervention group, the decision to operate remains with the surgical team and may be susceptible to influence from factors such as surgeon experience and preference, belief in the clinical equipoise and theatre availability. Participants in the non-surgical (standard care) group may still be reviewed for surgical intervention based on clinical need identified by their clinical team, as determined by current practice. In order to assess the effect of this limitation, quantification and analysis of adherence to randomisation is an important outcome of this feasibility study.

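### RMDQ precision is stated for all 43 completers, although the protocol's own rule means participants lacking capacity give no RMDQ score

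*Protocol article*

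**What the plan says.** All references are to the protocol article.

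- **Study procedures (text under Figure 1):** "For those participants that lack capacity, only clinically assessed questionnaires will be used".
- **Outcomes measures for the subsequent definitive trial:** the RMDQ is one of two primary measures, the other being the Timed Up and Go test (TUG). It is described "as a self-rated measure of physical disability caused by low back pain".
- **Recruitment and Discussion:** people who cannot consent for themselves are enrolled through a relative or carer acting as consultee. The reason given is that "it would severely affect the validity of the trial to exclude them".
- **Sample size calculation:** 48 recruited and 10% attrition give 43 completers. On that number the section gives "an SE of 0.9 for the RMDQ, assuming the SD is about 6 (95% CI 4.9 to 7.6"). The TUG figures use the same 43. Attrition is the only reduction applied.
- **Objectives:** estimating the mean and SD of the mobility, pain and quality-of-life measures, for use in planning the definitive trial, is one of the aims.
- **Data analysis:** completeness is to be tabulated per arm and in total.

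**The concern.** Two statements combine into a rule that the sample size section does not take into account. If only clinically assessed questionnaires are used without capacity, and the RMDQ is self-rated, then the RMDQ is absent by design for a group the trial has chosen to include. Counting that group among those who supply an RMDQ overstates the information the trial will yield on that measure.

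Two things are at stake. First, the SE and the SD interval are narrower than the design can deliver. Second, and more important, the RMDQ mean and SD will come only from participants with capacity. The SD is meant to feed the definitive sample size, so a reader could carry a figure from one part of the cohort over to the whole of it. In addition, completeness shown only by arm and overall would mix scores that were never to be collected with scores that were sought and not obtained. That would make the RMDQ look less acceptable to participants than it is.

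A later analysis plan cannot repair this, because it cannot recover scores that the protocol says will not be taken.

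**Working it through.** **Inputs from Sample size calculation.** The section says "we expect to screen approximately 100 patients", of whom 20% are ineligible and 60% of the rest are recruited. Attrition is 10% and the assumed RMDQ SD is 6.

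**Step 1: reproduce the plan's figures.**

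- Recruited: 100 × 0.80 × 0.60 = 48. Completers: 48 × 0.90 = 43.2, taken as 43.
- SE of the mean = SD/√n = 6/√43 = 0.915 (stated 0.9).
- 95% interval for the SD = SD × √[(n−1)/χ²], using the 97.5% and 2.5% chi-square quantiles on n−1 = 42 degrees of freedom. This gives 4.95 to 7.63 (stated 4.9 to 7.6).
- TUG on the same n: 8/√43 = 1.22 s, interval 6.60 to 10.17 (stated 1.2 s; 6.6 to 10.2).

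Every figure agrees, so the calculation is correct for 43 observations.

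**Step 2: apply the capacity rule.** Let f be the share of the 43 completers who lack capacity. The number with an RMDQ is n = 43 × (1 − f), rounded. The document does not give f, so the values below are assumptions.

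| Assumed f | n with RMDQ | SE = 6/√n | 95% interval for an SD of 6 |
|---|---|---|---|
| 0 (as in the plan) | 43 | 0.91 | 4.9 to 7.6 |
| 10% | 39 | 0.96 | 4.9 to 7.7 |
| 20% | 34 | 1.03 | 4.8 to 7.9 |
| 33% | 29 | 1.11 | 4.8 to 8.1 |
| 50% | 22 | 1.28 | 4.6 to 8.6 |

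**Step 3: find where the stated SE fails.** At n = 40, 6/√40 = 0.949, which still rounds to 0.9. At n = 39, 6/√39 = 0.961, which does not. The stated SE is therefore lost once four of the 43 have no RMDQ.

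**Step 4: what this adds to planning uncertainty.** For a comparison of means, required sample size scales with SD². At the upper limit of the SD interval, the multiple of the size planned on SD 6 is (7.63/6)² = 1.62 with all 43 scores, (7.90/6)² = 1.73 with 34, (8.11/6)² = 1.83 with 29 and (8.57/6)² = 2.04 with 22. Most of the inflation is already there at 43. Only the excess over 1.62 belongs to this point.

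**The case against.** The strongest reply is that nothing has been miscalculated, the loss is probably modest, and the trial exists partly to learn about completeness. Much of that stands. The figures reproduce exactly for 43. At 10% to 20% lacking capacity the SE moves only to 0.96 to 1.03, and even at 33% the 29 scores lie within the 24 to 50 that the protocol cites for a feasibility study. The Discussion concedes that cognitively impaired participants may complete less data, and completeness of the proposed measures is a listed secondary feasibility outcome. No primary feasibility outcome is touched.

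The reply does not remove the point. The Discussion speaks of engagement, recall and loss to follow-up. It does not say that the RMDQ is ruled out for these participants from the start.

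Several stronger readings are tempting, but the document does not support them:

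- **That QALYs exclude the same group by rule.** The outcome list has "EuroQol 5 Dimensions (EQ-5D-3L) Score^48^ as an assessment of quality of life", and Health economic analysis says "Effectiveness will be captured using quality adjusted life years (QALYs) as assessed by the EQ-5D-3L". Neither says whether the participant, an interviewer or a proxy completes it, and the schedule in Figure 2 is not shown. The completion mode is unclear; exclusion is not shown.
- **That up to two thirds of RMDQ scores will be missing.** The Discussion says "Cognitive impairment is common (up to 67%) in older patients presenting to hospital with PFF", and the Introduction puts impairment at more than a third. Both figures concern cognitive impairment among presenting patients, not incapacity among those enrolled. Under Recruitment, a low Abbreviated Mental Test score only triggers a capacity assessment, and the Discussion expects the consultee route to reduce recruitment of this group.
- **That these participants contribute almost nothing after week 2.** Survival, length of stay, readmission and adverse events are followed at each time point, resource use also comes from databases, and some week 12 contacts are face to face.
- **That the missing scores will differ by arm.** Delirium is named as a complication, so capacity could change during follow-up, but nothing in the document shows an imbalance.

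**Conclusion.** The point holds in a limited form. Two statements in the protocol mean that the RMDQ will not be collected from participants who lack capacity, while the stated RMDQ precision assumes that all 43 completers provide it. The figures are correct for their stated n and optimistic for the design.

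Over an assumed 10% to 50% lacking capacity, the SE is 0.96 to 1.28 against a stated 0.9, and the upper limit for the SD is 7.7 to 8.6 against 7.6. The range assumes that the SD stays at 6 among those with capacity and that capacity status is fixed. The share applies to completers: if people without capacity drop out more often, as the Discussion suggests they may, they form a smaller part of the 43 than of those recruited.

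The loss of precision is small if the share is low. The larger consequence is one of scope: the RMDQ mean and SD will describe participants with capacity, and nothing in the document says so. TUG is not a questionnaire and is not affected by this rule.

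**What to change.** 1. In Sample size calculation, state an assumed share of completers lacking capacity, with a range, and give the RMDQ SE and SD interval for the reduced number. Leave the TUG figures as they are.
2. Report completeness, mean and SD of the proposed outcomes by capacity status. For the RMDQ, count scores absent by rule separately from scores sought and not obtained.
3. State that any definitive sample size built on the RMDQ SD applies to participants with capacity.
4. State how the EQ-5D-3L is completed for participants lacking capacity.

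The cost is a few sentences and one extra breakdown in the tables. The stated RMDQ precision becomes slightly less favourable. No new data collection is needed for items 1 to 3, beyond keeping capacity status as an analysis variable. Choosing an observer-rated measure as the primary, or adding a proxy quality-of-life form, would be a wider design trade-off and is not needed to correct this point.
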